#### Missing data

We will describe the amount of missing data for covariates. For the multivariable logistic regression, we will assume that any missing data occur randomly between the study phases and intervention and control groups and will impute missing values 10-fold using chained equations. Results will be pooled according to Rubin’s rule.

### Data analysis strategy: workstream 2

We will use the RE-AIM framework,^14 15^ supplemented by the CFIR^16^ and the FIF,^17^ to examine implementation of the care bundle, mechanisms of impact and the impact of contextual factors, to map the ‘how’ and ‘why’ underpinning the results of the quantitative evaluation undertaken in workstream 1. These frameworks bring together metrics for evaluating implementation success, and by assessing reach and effectiveness the frameworks can be used together to identify ways to produce sustained changes (RE-AIM and FIF), which will highlight modifiable factors that explain and enhance implementation outcomes (CFIR). We will triangulate data from the NNRD, case report forms, and parent and HCP questionnaires and interviews to address the five evaluative dimensions of RE-AIM and map the CFIR constructs and FIF checklist within these domains (as appropriate; eg, particularly around Adoption, Implementation and Maintenance), to understand factors impacting implementation:

Reach: We will present information on numbers and percentages of infants and parents exposed to different elements of the care bundle and any exceptions or exclusions, considering variation by socioeconomic and demographic characteristics. We will measure numbers of HCPs trained to deliver the care bundle and perceptions of the acceptability and usefulness of training.Efficacy: In addition to the overall efficacy assessment in workstream 1, we will measure the efficacy of key components of the care bundle and investigate their impact on individual-level outcomes. For example, we will compare rates of own mother’s milk feeding between mothers who received antenatal breast feeding counselling and mothers who did not.Adoption: With HCPs and unit leads, we will explore the contextual factors that vary between units that may impact adoption and fidelity of recommended practices, using the FIF checklist and CFIR to guide thematic coding. Moderators of adoption and fidelity may include staff training and existing expertise, level of available resource locally.Implementation: We will explore factors that may affect implementation of the care bundle using CFIR as a coding framework. This will include factors related to the care bundle (eg, its complexity and evidence base), factors related to setting (eg, staff capacity to deliver the care bundle, availability of resources, time and expertise and leadership buy-in), attributes of roles within the teams and their motivations to implement the care bundle, and if and how the care bundle is adapted in each setting. This will help us better understand barriers and facilitators to implementation of the bundle.Maintenance: We will assess the extent to which the care bundle is embedded in training, policy and guidance.

Interview data will be analysed using the framework approach,^35 36^ a hierarchical, matrix-based method to map thematic differences/similarities within and between groups. First, a priori codes relating to the RE-AIM domains (Adoption, Implementation and Maintenance) will be applied to the data. Transcripts will then be coded again to apply the CFIR domains, constructs or subconstructs and FIF checklist (identified to influence RE-AIM domains), inductively. As an initial step to check validity of coding, two researchers will compare coding of several transcripts to reach consensus on interpretations. The remaining data will then be coded according to the relevant RE-AIM, CFIR and FIF code domains and construct codes, and the generated themes, with matrices of results and quotes presented and discussed among the full research team, to agree on data interpretation and the final themes.

### Sample size calculation

Workstream 1: The ITS analysis will have approximately 90% power to detect an absolute increase of 20% in the prevalence of receiving own mother’s milk at discharge and 80% power to detect a 15% absolute increase (baseline prevalence approximately 55%, approximately 23 infants per month in the EMNODN from 2017 to 2019; national average c.60%). This target is comparable to the prevalence of own mother’s milk feeding in the best performing neonatal network—in 2021, the South London Neonatal Operational Delivery Network achieved a prevalence of 76% (range by unit 71–80%) of infants receiving own mother’s milk at discharge.^37^ In 21 neonatal units in the UK in 2021, over 75% of infants received own mother’s milk at discharge, with the highest performing unit achieving 86% prevalence.^37^

NEC is a rare occurrence (incidence approximately 7%, approximately 3 cases per month in the EMNODN from 2017 to 2019; national average c.5%), and there is also considerable monthly variability in incidence. Therefore, statistical power to detect small changes in the incidence of NEC will be more limited; we will be powered to detect approximately a two-thirds reduction in the incidence of NEC. In line with previous studies of less common neonatal outcomes,^27^ the point estimate will, however, give an indication of the effect of the care bundle, even if the CI around this point estimate crosses the null value.

Workstream 2: We aim to conduct 33 interviews with parents (either individuals or couples, 3 per EMNODN unit) and 33 interviews with HCPs (3 per unit) using a combination of convenience (self-selecting) and purposeful sampling approaches, the latter particularly to approach parents from underserved groups who usually hesitate to participate in research. These numbers are based on principles of maximum variation and theoretical data saturation, which is related to the sampling approach rather than the analysis.^38^ Preliminary analysis will inform whether we need to use a second strategy based on the notion of inductive thematic saturation^39^ and, in which case, we may need to conduct additional interviews.

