## Introduction

Necrotising enterocolitis (NEC) is a serious, life-threatening disease in preterm infants.^1^ An estimated 12% of infants born weighing <1500 g develop NEC and 30% of these die.^2^ Survivors have increased risk of adverse neurodevelopmental outcomes, including cerebral palsy and cognitive impairment.^3^ Encouraging and supporting own mother’s milk feeding prevents NEC and has several additional advantages, including improved long-term neurodevelopment and parent–infant bonding.^4^ Health economic analysis estimates that if all premature infants were to be fed own mother’s milk, the total lifetime cost saving to the National Health Service (NHS) would be £46.7 million (£30.1 million in the first year of life), and there would be 238 fewer deaths per year with a gain of £153.4 million in lifetime productivity.^5^

Neonatal critical care services in England are commissioned by NHS England and managed within 11 neonatal operational delivery networks, to ensure that babies and their families receive high-quality, equitable and accessible care. The East Midlands Neonatal Operational Delivery Network (EMNODN^6^) comprises 11 neonatal units across seven NHS trusts, covering an area of 15 627 km^2^, a total population of approximately 4.9 million^7^ and approximately 47 000 live births per year.^8^ In 2022, EMNODN units provided 50 443 days of care in total to infants born preterm, or unwell at term, who needed specialist neonatal care; 476 infants were cared for who were born before 32 weeks’ gestational age (GA) and survived at least 48 hours.^9^

The rate of NEC in the EMNODN has remained above the national average since 2017, when this measure was added to the National Neonatal Audit Programme (NNAP).^10^ Additionally, there are wide variations between the 11 units that comprise the EMNODN. Rates of any breastmilk feeding at discharge from EMNODN units have been consistently below the national average, again with wide local variations.

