### Time period

1 January 2016 to 30 September 2023, with infants grouped by date of birth into three groups according to date of implementation of the care bundle: pre-implementation period—1 January 2016 to 31 August 2022; implementation period—1 September 2022 to 31 December 2022; evaluation period—1 January 2023 to 30 September 2023, followed up for 3 months (until 31 December 2023) to cover the full neonatal stay of the final participant.

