#### Multiple testing

IRRs for the primary and secondary outcomes will be reported with 95% CIs and Bonferroni-corrected p values.

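### The two power figures for own mother's milk at discharge do not fit together if they describe one test at one alpha, and nominal 95% CIs are paired with Bonferroni-corrected p values

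*Protocol article*

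**What the plan says.** The Sample size calculation section of the protocol article makes two statements about the interrupted time series (ITS) analysis of own mother's milk at discharge. The first is "approximately 90% power to detect an absolute increase of 20% in the prevalence of receiving own mother’s milk at discharge". The second, in the same sentence, is "80% power to detect a 15% absolute increase (baseline prevalence approximately 55%, approximately 23 infants per month". Outcome, baseline and data set are common to both. The section gives no alpha, sidedness or dispersion, and does not say whether the step term or the slope-change term is tested. The analysis strategy for workstream 1 includes both terms in a quasi-Poisson model and reports an incidence rate ratio (IRR).

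Under Multiple testing, IRRs for the primary and secondary outcomes "will be reported with 95% CIs and Bonferroni-corrected p values". The number of tests in the correction is not given. The article lists three primary and two secondary outcomes.

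**The concern.** For a given test, power at one effect size fixes power at every other. Two stated power figures for the same analysis can therefore be checked against each other without knowing how they were obtained. Here the step from 15 to 20 points is too large for a rise from 80% to only 90%. At least one figure is then off, or the two rest on different assumptions that are not stated.

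Two further matters affect how the results will be read. The planned p values are Bonferroni-corrected, so power at an uncorrected 0.05 would not be the power of the test that is reported. In addition, a CI at one level beside a p value at another can give two different answers on significance for the same outcome, including a primary one. The Sample size calculation section itself discusses the NEC result in terms of whether the CI crosses the null, so readers are likely to use the CI in that way.

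**Working it through.** **Inputs from the protocol article.** Baseline 55%; rises to 70% and 75%; stated power 80% and about 90% (Sample size calculation). The effect scale is an IRR (Data analysis strategy: workstream 1). Three primary and two secondary outcomes.

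**Assumptions, because the article does not give them.** Two-sided alpha 0.05, and one standard error (SE) for both effects. The number of tests k is 3 (primary outcomes only) or 5 (all outcomes).

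**1. Are the two figures compatible?** Power = Φ(effect/SE − z), with z = 1.960.
- 80% power needs effect/SE = 1.960 + 0.842 = 2.802.
- 90% power needs effect/SE = 1.960 + 1.282 = 3.242.
- Required ratio of effects: 3.242/2.802 = 1.157. If +15 has 80% power, 90% is reached at 15 × 1.157 = 17.4 points.

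The ratio of the stated effects is larger on every scale tried:

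| Scale | Ratio, +20 to +15 | If 80% at +15, power at +20 | If 90% at +20, power at +15 |
|---|---|---|---|
| Log IRR | 0.3102/0.2412 = 1.286 | Φ(2.802 × 1.286 − 1.960) = 95% | Φ(3.242/1.286 − 1.960) = 71% |
| Absolute difference | 20/15 = 1.333 | 96% | 68% |
| Logit | 0.898/0.647 = 1.389 | 97% | 65% |

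Other alphas do not close the gap. At two-sided 0.10, 0.05/3 and 0.01, the implied power at +20 is 94–98.5% and the implied power at +15 is 58–74%. Nor does rounding: at 0.05 the best compromise SE still leaves each figure 3 points off (log IRR: 77% and 93%) to 5 points off (logit: 75% and 95%).

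**2. Can the plan's own figures be reproduced?** A segmented Poisson model was tried with 80 pre-implementation months ("pre-implementation period—1 January 2016 to 31 August 2022") and 9 evaluation months. The monthly denominator was taken as 40–42 infants. This is inferred from 23/0.55 = 41.8 (reading 23 as infants with the outcome) and from 476/12 = 39.7 (the Introduction: "476 infants were cared for who were born before 32 weeks"). It also agrees roughly with 3/0.07 = 43 from the NEC figures ("incidence approximately 7%, approximately 3 cases per month in the EMNODN from 2017 to 2019").

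| Model, tested term = step | Alpha | Power at +15 | Power at +20 |
|---|---|---|---|
| Trend + step, Poisson variance | 0.05 | 81–84% | 96–97% |
| Trend + step, Poisson variance | 0.01 | 60–64% | 87–90% |
| Trend + step + slope change, Poisson variance | 0.05 | 34–39% | 53–61% |
| Trend + step + slope change, binomial variance | 0.05 | 76–85% | 96–99% |

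The first row comes close to the stated 80% but not the stated 90%; the second can match the 90% but not the 80%. No single model and alpha tried gave the pair within 2 points. The wide spread shows how much depends on the tested term and the variance, neither of which the power statement names.

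**3. What would the correction do if the stated figures assume 0.05?** Replace z = 1.960 by 2.394 (0.05/3) or 2.576 (0.05/5).
- Three tests: Φ(2.802 − 2.394) = 66% and Φ(3.242 − 2.394) = 80%.
- Five tests: Φ(2.802 − 2.576) = 59% and Φ(3.242 − 2.576) = 75%.

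**4. When do the CI and the corrected p value disagree?** A 95% CI excludes 1 when the raw p is below 0.05. The corrected p is k × raw p, and is below 0.05 only when the raw p is below 0.05/k. They disagree for a raw p from 0.0167 to 0.05 (k = 3, corrected p up to 0.15) or from 0.01 to 0.05 (k = 5, corrected p up to 0.25). For example, a raw p of 0.03 gives a CI that excludes 1 beside a corrected p of 0.09 or 0.15. The matching CI level is 1 − 0.05/k: 98.3% for three tests, 99% for five.

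**The case against.** The article is condensed. Alpha, tested parameter and method may be set out in a fuller document, and the 90% is stated as approximate. The incompatibility therefore depends on both figures describing one test at one alpha. That condition stands, although it is the natural reading of a single sentence about a single analysis.

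A reader might infer more than the article supports in three ways.
- **That the power is overstated.** This does not follow. If 80% at +15 is the correct figure, then about 90% at +20 is an understatement and errs on the cautious side. The article does not show which figure is the anchor, and the reconstructions range too widely to decide it.
- **That neither figure allows for the Bonferroni correction.** Silence on alpha does not show this. In the step-only Poisson model, the 90% at +20 fits alpha 0.01 (87–90%) better than 0.05 (96–97%).
- **That CIs and p values will contradict each other.** They can do so only within the range of raw p shown above. The estimate and its direction are the same either way; only the significance label differs.

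It is also fair to say that this is a retrospective cohort over fixed dates, so restating power changes neither the sample nor any estimate, and that limited power for NEC is already disclosed. Bonferroni over all reported outcomes is a valid choice, and nothing here calls for another procedure.

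**Conclusion.** The point holds in conditional form. For one test at one alpha, the two power figures are inconsistent by about 5–7 percentage points at +20 (95–97% against about 90%) or about 9–15 points at +15 (65–71% against 80%). This rests on a common SE and two-sided 0.05; the gap remains at the other alphas tried. Which figure needs correcting cannot be settled from the article.

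The loss of power from the correction, to 66%/80% or 59%/75%, applies only if the stated figures assume 0.05 and k is 3 or 5. The mismatch between nominal CIs and corrected p values needs no such assumption. It follows from the stated reporting rule whenever more than one test is corrected for, and it can affect a primary outcome.

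**What to change.** Recompute both power figures and restate them for one named parameter (step or slope change), at the alpha at which that parameter will actually be tested, and state that alpha and the number of tests in the correction. Under Multiple testing, report CIs at the level that matches the corrected test (98.3% for three tests, 99% for five) beside nominal 95% CIs labelled as unadjusted.

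The cost is a recalculation, a few sentences of wording, and possibly a less favourable stated power. No data, eligibility rule or analysis model changes.

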## Patient and public involvement

The study protocol has been co-produced with the EMNODN Parent Advisory Group and the parent-led charity NEC UK^40^ to ensure representation from those with lived experiences of NEC and its consequences, both in the neonatal unit and after discharge. The chair of NEC UK is a parent co-applicant and will lead patient and public involvement (PPI) activities. A second PPI representative will also be invited to join the Project Management Group.

The primary outcome of receiving own mother’s milk feeds at discharge was selected by the parents as being the most meaningful outcome for them, and, further to their advice, the emphasis on receiving information and support for breastmilk expression in the process evaluation and the plans to explore this in detail in the semistructured parent interviews were included in the study plan.

With the support of The Centre for Ethnic Health Research,^41^ a semistructured focus group discussion has been conducted with women representing different ethnic minority groups, all of whom had experience of having a preterm baby. This discussion focused on co-production of study documentation, particularly the participant information sheets and interview guides. A semistructured focus group discussion has also been conducted with HCPs working with preterm infants in the East Midlands. This discussion focused on the production of the interview guide for HCPs. Interested parties from both focus groups will be invited to validate qualitative analyses (respondent validation), comment on results and recommendations and review and revise the public-facing dissemination materials. A final parent-led dissemination meeting will be held within the EMNODN.

## Ethics and dissemination

The study is sponsored by the University Hospitals of Derby and Burton NHS Foundation Trust and has been registered on the ClinicalTrials.gov database (Ref: NCT05934123). The study has been approved by the South East Scotland Research Ethics Committee 01 and the Health Research Authority and Health and Care Research Wales (IRAS 323099). We will use the Reporting of Studies using Observational Routinely Collected Data (RECORD) checklist,^42^ an extension of the Strengthening the Reporting of Observational Studies in Epidemiology guidelines,^43^ to ensure transparency of reporting of our methods and results. On completion of the study, findings will be disseminated via: a detailed report for National Institute for Health and Care Research as well as the EMNODN and participating neonatal units; public-facing materials (infographics, animated video) in English, Polish, Gujarati and Punjabi (the most frequently spoken languages in the East Midlands), created and shared via parent groups and directly with study participants; open access, peer-reviewed journals and scientific conferences; and dissemination to relevant specialised commissioners including the NHS England Neonatal Critical Care Clinical Reference Group.

## Discussion

National recommendations cite a need for QI efforts to increase own mother’s milk feeding to reduce NEC.^44^ In 2020, NNAP recommended that if rates of NEC are relatively high, neonatal networks and units should ‘seek to identify and implement potentially better practices’ and to ‘focus on the early initiation and sustainment of breastmilk feeding in conjunction with parents by reviewing data and processes’ and ‘undertake selected QI activities suited to the local context’.^44^ This multicomponent evaluation of the care bundle developed for use in the East Midlands will provide evidence to help understand whether the bundle should be rolled out nationally and what changes might be needed to ensure optimum impact and successful implementation within local contexts. Thus, the findings of this study have the potential to improve patient care in the EMNODN and wider, with direct benefits to preterm infants and their families. The parallel effectiveness and process evaluations will establish a framework and toolkit for evaluation of other similar QI initiatives in future.
